### Data collection procedures and methods

Baseline clinical data will be collected from 30 medical records of hospitalized infants by a trained research nurse or research assistant at each site before randomization at all NICUs (T1). If there are > 30 infants in the NICU, infant medical records will be randomly selected using a computer-generated random sequence. The ACT survey will be electronically distributed to all NICU nursing staff within each unit at baseline (T1). Two reminders will be sent out using the same methods at two-week intervals.

#### Intervention (INT) group

Three to five eligible HCPs within each NICU that is randomized to the INT group will be invited to participate on that NICU’s Change Team. Once identified and consented, each NICU group will receive a 1-h in-depth standardized training session on the Resource. At this session, Change Team members will be asked to complete the ACT survey and will be provided an individual login to access the Resource. The session will be delivered by a member of the lead site research team either in person (preferable) or by distance using a video conference program (e.g. Zoom).

During the six-month INT, the Change Team will independently navigate through the seven steps of the Resource with no implementation support from the lead research team. The lead site research staff will be available for questions should they arise but will not contact the site or provide implementation coaching; this distancing is important with respect to establishing external validity and sustainability of the Resource in the long term.

At the completion of the six-month INT, clinical data for 30 infant medical records in the NICU will be collected at each data collection point (T2–T4) by a trained research nurse or research assistant who is not involved in the implementation of the Resource. Implementation outcome data will be collected from metrics captured within the Resource and through semi-structured focus groups with Change Team members (one focus group per site), as described in Table 1. Focus groups will be conducted at each site in person (preferable) or via video conference by a trained facilitator from the lead site using an interview guide (Table 1). The Change Team will be encouraged to continue to use the Resource after the six-month INT.

#### Standard Practice (SP) group

Following randomization, units in the SP group will be advised to continue with their usual pain practices for six months.

Following data collection at T2, the SP units will be invited to use the Resource. They will follow the same procedures described for the INT group in terms of recruiting and training the Change Team members. The Resource will be monitored and evaluated in the same way as for the INT group. Data on clinical and implementation outcomes will be collected after a six-month period (T3); however, focus groups will not be conducted for units in the SP group.

Six months after completion of the Resource intervention (T4), data from 30 infant medical records per NICU will be collected. Resource metrics will also be examined.

Quantitative data (clinical, demographic, and organizational context data) will be collected and managed using Research Electronic Data Capture (REDCap™). Steps to promote data quality will be undertaken, including regular database review and range checks on data values. Implementation outcome data captured from embedded Resource metrics (e.g. feasibility, fidelity, implementation costs, and sustainability) will be captured and stored by the Resource website.

### Contamination and co-intervention

To avoid intervention contamination, we will use a cluster RCT with the hospital NICU as the unit of randomization. Where two or more eligible NICUs are co-located in one hospital or within one hospital organizational structure where there is significant overlap of staff and management, both sites will be randomized to receive the same intervention and will be counted as one NICU site for the purposes of the study analyses.

Co-intervention may occur if either group receives additional implementation strategies to improve practice and clinical pain outcomes (e.g. a hospital-based strategy to reduce procedural pain in infants) through initiatives outside the study. We will not interfere with any hospital-initiated activities that promote improvement in pain assessment or management within the NICU or the hospital during the trial. This information will be documented in focus groups following completion of the six-month INT. We will ask the SP groups to document this activity.

### Data management, analyses, and monitoring

#### Quantitative data

All primary analyses to determine intervention effectiveness will be conducted as intention to treat. The characteristics of infants admitted to participating NICUs and enrolled in the study will be summarized using descriptive statistics such as means and SD for continuous variables and medians and ranges for categorical variables. Given the lack of independence in outcomes due to sampling of multiple patients from the same NICU, inferential statistical methods that account for this clustering will be used. To assess the impact of the Resource on the clinical outcomes (proportion of infants with any validated pain assessment used and any pain management strategy used), the odds of a particular outcome will be compared between INT and SP groups as the odds ratio with 95% confidence interval and *p* value. Parameter estimation will be facilitated by a logistic regression model, with the clustering by NICU accomodated by estimation using Generalized Estimating Equations. The impact of contextual factors on clinical outcomes will be explored. Generalized estimating equation models for binary outcomes (i.e. logit link) will model implementation outcomes in both groups while including contextial covariates. All models will be assessed for goodness-of-fit. Imputation for missing data will be employed only if there is > 10% of missing data. Comprehensive training and database monitoring will be performed to minimize potential loss of data; in a previous study in which similar data was collected [16], missing data were minimal (< 5%). All analyses will be conducted using SAS v9.4 (Cary, NC, USA).

Analysis of implementation costs will be captured within Resource metrics which include quantifying resources required for its implementation over a six-month period—including: human resources (time spent on orientation and training, navigation through the Resource, meetings among Change Team members, implementation of the Resource either individually or in groups); equipment (e.g. laptop); materials (e.g. printing materials); and other related expenses—and will be captured by the Resource (Steps 5 and 7). The uncertainty of the findings will be explored. This analysis can provide evidence to inform scalability and sustainability of the Resource.

For organizational context data, descriptive statistics (e.g. means, SD) for each of the 10 ACT concepts will be reported. Outcome means for each NICU will be compared to the overall sample. We will also categorize the NICUs in a binary manner as high or low using quartiles. Analysis of variance and multiple comparison tests will be used to investigate differences in workplace environment characteristics relative to primary outcomes. If an adequate sample size is not achieved, then non-parametric methods (e.g. Kruskal–Wallis test) will be used. Regression modeling will be used to assess the influence of organizational factors on clinical pain practices to determine if units with more positive organizational context scores are more successful in adopting the resource and have more positive pain management practices.

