### Sample size

Data will be collected from 30 medical records of infants in each NICU. Assuming an inter-class correlation coefficient of 0.2, the variance inflation factor due to the cluster design is 6.8. With 16 NICUs, there will be an 80% power to achieve statistical significance at the 5% level, two-sided if the treatment arms differ by 0.67 standard deviations (SD; between-patient, within cluster), representing a moderate effect-size. Using estimates from prior studies [7] this would yield detectable differences of 0.33 for the binary outcome *pain assessed with a valid instrument*, and 0.27 for the binary outcome *any pain management*. A dropout rate of 10% of the sites is anticipated, therefore 18 units will be enrolled.

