### Recruitment and assignment

Eligible level 2 and level 3 NICUs in Canada will be invited to participate via email from the lead research team to the Unit Manager and Medical Director, detailing a brief introduction to the study and recruitment video that will inform on study objectives, design, and timelines. Sites that express interest in participating will be offered a site visit to learn further details of the study. Once participation is confirmed, the recruited sites will receive assistance in applying for local institutional research ethics board (REB) approval. Baseline data collection on infant medical records will commence once institutional REB approval is granted and financial subcontracts are completed.

Participating NICUs will then be randomized to groups using a computer-generated random allocation sequence (randomize.net). Randomization will be stratified by NICU level (level 2 or level 3). Once units are randomized to the INT group, eligible HCP staff will be recruited to participate as a Change Team member and all eligible unit staff will be asked to complete the ACT. The Change Team for the SP group will be recruited and offered the ImPaC intervention after the six-month waiting period after unit randomization.

Data analysts will be blinded to group allocation. Change Team and NICU staff will not be blinded due to the visible nature of the intervention.

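### The primary model should say that the comparison is at T2 and adjust for each NICU's pre-randomization (T1) outcome and for NICU level: a cheap gain in precision, not a correction of bias

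*Protocol article*

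**What the plan says.** All references are to the protocol article.

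- **Primary analysis** (Data management, analyses, and monitoring, Quantitative data): "the odds of a particular outcome will be compared between INT and SP groups as the odds ratio with 95% confidence interval". The model is logistic, estimated by GEE with NICU as the cluster. No time point, baseline term, group-by-time term or stratum term is given. Contextual covariates are mentioned in the same paragraph, but only for the exploratory context work and the implementation models.
- **Baseline data** (Data collection procedures and methods): "Baseline clinical data will be collected from 30 medical records of hospitalized infants" at each site, before randomization. Clinical (primary) outcomes and Table 1 list T1 and T2 as time points of every primary outcome in both groups.
- **Design** (Study design, text after Fig. 1): the primary outcomes are to be assessed between the groups both pre- and post-intervention. No method is attached.
- **Randomization** (Recruitment and assignment): stratified by NICU level, 2 or 3.
- **Sample size**: "Assuming an inter-class correlation coefficient of 0.2, the variance inflation factor due to the cluster design is 6.8". The calculation takes 16 units, a two-sided test at 5% and a power of 80%, and arrives at a detectable difference of 0.67 SD. No allowance for a baseline measurement appears.

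**The concern.** The trial randomizes 18 units and is powered on 16. With an ICC of 0.2, most of the variance of a NICU mean lies between NICUs. The T1 charts measure the same outcome in the same NICUs before allocation, so they can account for whatever part of that variance is stable over six months. As written, the primary model does not use them.

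The text can also be read as at least three different analyses:

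- T2 only, unadjusted.
- T1 and T2 together with a group-by-time term, which is in effect a change-score comparison.
- T1 and T2 pooled with a group term only, which mixes pre-intervention data, where the true difference is zero, into the estimated effect.

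With so few clusters these can give noticeably different answers, so the choice should be fixed in advance. At stake are the width of the confidence interval and the power, not the validity of the randomized comparison.

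**Working it through.** **Inputs from the article:** 16 NICUs; 30 charts per NICU per time point; ICC 0.2; two-sided 5%; 80% power; detectable difference 0.67 SD, stated as 0.33 (pain assessed) and 0.27 (pain management).

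**Assumptions:** 1:1 allocation, so 8 NICUs per arm (the ratio is not stated). SD is taken as the total SD, the reading under which the stated figure reproduces. The cluster autocorrelation *c* is the correlation of a NICU's underlying level between T1 and T2; the document does not give it, so it is varied. The infants at T2 are taken as a new sample.

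**1. The article's own figure**

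- Variance inflation = 1 + (30 − 1) × 0.2 = 6.8.
- Effective n per arm = 8 × 30 / 6.8 = 35.29.
- Standard error = √(2 / 35.29) = 0.238 SD.
- Detectable difference = (1.960 + 0.842) × 0.238 = 0.667 SD.

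The stated 0.67 therefore reproduces as an unadjusted comparison at one time point. With a t reference on 14 degrees of freedom, power at 0.67 SD is 74.5%.

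**2. How informative T1 can be**

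- Reliability of a NICU's T1 mean = 30 × 0.2 / 6.8 = 0.882.
- Correlation of T1 and T2 NICU means: r = 0.882*c*.
- Variance relative to T2 only: adjusted for T1, 1 − r²; change score, 2(1 − r).

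| *c* (assumed) | r | 1 − r² | Detectable difference (SD) | Power at 0.67 SD, T1-adjusted, 13 df | Plus NICU level, 12 df | 2(1 − r) |
|---|---|---|---|---|---|---|
| 0 | 0 | 1.000 | 0.667 | 74.0% | 73.4% | 2.000 |
| 0.5 | 0.441 | 0.805 | 0.598 | 82.6% | 82.1% | 1.118 |
| 0.7 | 0.618 | 0.619 | 0.524 | 91.1% | 90.7% | 0.765 |
| 0.8 | 0.706 | 0.502 | 0.472 | 95.6% | 95.3% | 0.588 |

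At *c* = 0.8 the variance roughly halves; the stated 0.33 and 0.27 would become about 0.23 and 0.19. A change score is worse than T2 only at *c* = 0.5 (variance 12% larger), and worse than T1 adjustment in every row.

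**3. Simulation check**

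Cluster-level linear analysis, 6,000 runs per setting. Power at 0.67 SD was about 75% unadjusted, against 71%, 80% and 94% adjusted for T1 at *c* = 0, 0.5 and 0.8. Type I error was about 5% throughout. The adjusted figures are slightly below the table because the table counts the lost degree of freedom but not the cost of estimating the T1 slope.

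**4. Chance imbalance at T1**

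The SD of the difference between arms in T1 means is 0.238 SD. On the scale of pain assessed this is 0.238 × 0.33 / 0.67 = 0.117, and for pain management 0.238 × 0.27 / 0.67 = 0.096. The chance of an imbalance above half the detectable effect (0.335 SD) is 16%. Only a fraction r is expected to carry over to T2: a 0.23 imbalance (1.96 × 0.117) carries over as about 0.10 at *c* = 0.5 and 0.16 at *c* = 0.8.

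**The case against.** The strongest reply is that this is a condensed article. Lists of model terms are commonly left to an analysis plan, which is not shown, and nothing in the article excludes T1 or NICU level. A reader might infer that the trial will ignore its baseline data. The documents do not support that: it would be an inference from silence, and the design section and Table 1 point towards using both time points. What remains is that the article does fix the contrast, link and estimation method without these terms, sizes the trial as if they were absent, and does not reconcile this with its own pre- and post-intervention description.

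A reader might also infer that chance imbalance among so few NICUs biases the result. It does not. Between-NICU variance is already counted in the factor of 6.8, and size stayed near 5% with and without adjustment. Stratified randomization already limits imbalance in NICU level, so including the stratum is mainly a matter of matching analysis to design.

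Third, the gain is neither guaranteed nor free. It depends on an autocorrelation that the document does not give, and at zero there is a small loss. Each intervention NICU chooses its own practice target after auditing itself, which could weaken the T1–T2 correlation in that arm. The calculations are for cluster-level linear analyses, not the planned logistic GEE with 16 clusters. All of this stands and limits the strength of the point.

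**Conclusion.** The point holds as a recommended improvement. The stated primary model and sample size describe a comparison without T1 or NICU level, although both are known for every NICU before the intervention starts. If NICU practice is moderately to strongly stable over six months (assumed *c* of 0.5 to 0.8), adjusting for T1 cuts the variance by 19% to 50%. It also brings t-based power from 74.5% to above the planned 80% (82.6% to 95.6%; 80% to 94% in simulation). If T1 does not predict T2, power falls slightly, to 74.0% by formula and 71% by simulation.

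These sizes rest on the article's ICC of 0.2, 30 charts per NICU, 8 NICUs per arm and the assumed *c*. The lack of a baseline gain in the sample size is not an error.

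**What to change.** Add one sentence to the primary analysis text. It should state that each primary outcome is compared between arms at T2, with arm, NICU level and the NICU's own T1 summary as cluster-level covariates. The T1 summary could be the empirical logit of the T1 proportion for the binary outcomes and the T1 mean for the procedure count. State that the reported odds ratio is marginal, and that a simple change from baseline is not used.

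No new data are needed. The costs are up to two of 14 cluster-level degrees of freedom, a slight loss of power if T1 proves uninformative, and a standardisation step, because adding covariates to a logistic model otherwise moves the odds ratio towards a conditional one. The sample size can stay as it is.

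### With only 16–18 NICUs, the logistic GEE for the two binary primary outcomes needs a stated small-sample correction: ordinary Wald inference would reject about 8–10% (16 NICUs) or 7.5–9% (18) at a nominal 5%

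*Protocol article*

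**What the plan says.** Under Data management, analyses, and monitoring (Quantitative data), the effect on the two binary clinical outcomes, any validated pain assessment and any pain management, is an odds ratio with 95% confidence interval and p value. It comes from a logistic model "with the clustering by NICU accomodated by estimation using Generalized Estimating Equations". The software is SAS 9.4. The text names no variance estimator, small-sample correction, reference distribution or degrees of freedom. It states no model for the third primary outcome, the number of painful procedures.

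Under Sample size, the design is set out as follows:
- Each NICU contributes 30 charts.
- The intracluster correlation is taken as 0.2, which gives a design effect of 6.8.
- The power claim reads "With 16 NICUs, there will be an 80% power to achieve statistical significance at the 5% level". The test has two sides, and the difference between arms is set at 0.67 SD.
- Eighteen units are enrolled to allow for 10% site dropout.

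Under Recruitment and assignment, randomization is stratified by NICU level. No allocation ratio is given.

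**The concern.** The usual GEE sandwich variance and its normal reference are justified as the number of clusters grows. Here there are 8 or 9 NICUs per arm, and 30 charts per NICU do not make up for that. Two errors act in the same direction. The uncorrected sandwich variance is biased low, and the normal quantile ignores the uncertainty in a variance estimated from so few clusters. The test then rejects too often and the interval is too short. The conclusion at stake is the main one, that the Resource changes pain assessment or pain management.

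**Working it through.** **Inputs.** From Sample size: 30 charts per NICU, intracluster correlation 0.2, 16 or 18 NICUs, two-sided 5%, difference 0.67 SD, detectable differences 0.33 and 0.27. Assumed: 1:1 allocation (m = 8 or 9 per arm), equal clusters, comparison at T2 only, beta-binomial clustering.

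**1. The plan's own power figure.**
- Design effect = 1 + 29 × 0.2 = 6.8.
- Effective number per arm = 8 × 30 / 6.8 = 35.3.
- Standard error in SD units = √(2/35.3) = 0.238, and 0.67/0.238 = 2.81.
- With normal quantiles, power = Φ(2.81 − 1.96) = 80.4%.

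The stated 80% is reproduced, and it makes no allowance for few clusters.

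**2. Event rates implied by the plan.**
- 0.33/0.67 = 0.49 as the SD, so p is about 0.41 (or 0.59).
- 0.27/0.67 = 0.40, so p is about 0.20 (or 0.80).

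The check therefore covers p from 0.2 to 0.5; values above 0.5 mirror these.

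**3. Analytic approximation.** For two arms with equal clusters, the uncorrected sandwich variance is low by about (m − 1)/m. True size is about P(|t on 2m − 2 df| > 1.96 × √((m − 1)/m)).
- m = 8: P(|t14| > 1.96 × √(7/8)) = 8.8%, so coverage is 91.2%.
- m = 9: P(|t16| > 1.96 × √(8/9)) = 8.3%, so coverage is 91.7%.
- Interval width relative to the correct one is 0.855 (16 NICUs) and 0.872 (18), so about 15% and 13% too narrow.

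**4. Simulation under no effect.** 200,000 trials per row, intracluster correlation 0.2, 30 charts per NICU. Entries are rejection rates in %. KC is the Kauermann–Carroll and MD the Mancl–DeRouen correction; t has (NICUs − 2) df.

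| NICUs | Event rate | Uncorrected, z | Uncorrected, t | KC, z | KC, t | MD, t |
|---|---|---|---|---|---|---|
| 16 | 0.20 | 9.75 | 7.23 | 7.84 | 5.71 | 4.41 |
| 16 | 0.30 | 8.68 | 6.35 | 6.91 | 4.92 | 3.72 |
| 16 | 0.45 | 8.18 | 5.91 | 6.46 | 4.55 | 3.43 |
| 16 | 0.50 | 8.17 | 5.89 | 6.43 | 4.47 | 3.33 |
| 18 | 0.20 | 9.06 | 6.99 | 7.50 | 5.65 | 4.45 |
| 18 | 0.30 | 8.22 | 6.23 | 6.68 | 4.95 | 3.87 |
| 18 | 0.45 | 7.79 | 5.83 | 6.30 | 4.58 | 3.53 |
| 18 | 0.50 | 7.79 | 5.83 | 6.29 | 4.60 | 3.56 |

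A second simulation (100,000 trials per cell, event rates 0.2, 0.41 and 0.5) gave 8.0–9.7% with 8 per arm and 7.8–9.1% with 9 per arm, uncorrected. It gave 4.4–5.7% with a corrected sandwich and t reference. Either correction alone is not enough: the corrected variance with z, or the uncorrected variance with t, still rejects about 6–8%.

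**5. Fitted exchangeable GEE** (1,500 trials per cell, Monte Carlo error about 0.7 points, event rates 0.45 and 0.2).
- Uncorrected sandwich with z: 8.3% and 8.7% (16 NICUs), 7.5% and 8.1% (18).
- Model-based standard errors with z: 7.3–8.3% across both cluster counts.

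**6. Power with a t reference at 0.67 SD.**
- 16 NICUs: 74.5%, against 80.4% with normal quantiles.
- 18 NICUs: 80.0%, against 84.7%.

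**The case against.** The strongest objection is that this is detail an article leaves to the analysis plan. The article fixes the model, the estimation method, the clustering unit and the form of the result. It nowhere says that the variance is uncorrected or the reference normal. The stated software can apply the corrections, and nothing in the text contradicts their use. The result also depends on the choice left open: a GEE score test holds size at about 5.2–5.6% for event rates 0.2–0.5.

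Much of this stands. A reader might infer that the trial's primary test certainly runs at 8–10%. The article does not support that, because the analysis plan is not shown and may contain a correction. The power calculation is not wrong on its own normal-approximation terms either.

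It does not remove the point. The article pairs a large-sample method with 8 or 9 clusters per arm. Followed as written with standard GEE inference, it misses its stated level. Nothing suggests that a correction was assumed, since the 80% power reproduces with normal quantiles. For the organizational context data the same section offers non-parametric methods if the sample is too small, yet it gives the primary comparison no such safeguard. A score test would repair the p value but not a Wald confidence interval.

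Two further extensions go too far. Adjusting for NICU level alone raised the fitted-GEE size to 9.1–9.7% (16 NICUs) and 8.5–9.0% (18), but the article puts neither NICU level nor the baseline value in the primary model, so no larger figure belongs to the plan. The GEE is also stated only for the two binary outcomes; the procedure count is affected only if it too is analysed by GEE.

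**Conclusion.** The point holds in conditional form. Under ordinary GEE Wald inference the nominal 5% test has a true size of about 8–10% with 16 NICUs and 7.5–9% with 18, roughly 1.5 to 2 times the stated level. Nominal 95% intervals cover about 90–92%.

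This rests on 1:1 allocation, equal clusters of 30, a T2-only comparison and event rates of 0.2–0.5. It depends little on the intracluster correlation: at 0.05–0.1 the size is 8.4–9.1% (16) and 8.0–8.5% (18). At an event rate of 0.1 and correlation 0.2, which is outside what the plan's figures imply, it is 12.7% and 11.8%.

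**What to change.** For the two binary primary outcomes, and for the procedure count if GEE is used there, specify before unblinding:
- a bias-corrected sandwich variance, Kauermann–Carroll or Mancl–DeRouen, both available in SAS 9.4 through the EMPIRICAL= options of PROC GLIMMIX;
- a t reference with degrees of freedom equal to the number of NICUs minus the number of NICU-level parameters (14 with 16 NICUs and 16 with 18 in the two-arm model), for both p value and interval.

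The Kauermann–Carroll type holds size at about 4.4–5.7%. Mancl–DeRouen is mildly conservative here (3.3–4.5%). At an event rate of 0.1 neither fully restores the level (about 8% and 6.3%). A permutation test stratified by NICU level is an optional confirmation. If the analysis plan already contains such a correction, one sentence in the protocol saying so is enough.

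No new data are needed, but there is a cost beyond wording. Intervals become somewhat wider, and the Sample size section should restate power at 0.67 SD as about 74% with 16 NICUs and 80% with 18. The stated 80% is then kept only if no site drops out.
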